### Evaluation of implementation

#### Design

Adherence to the intervention will be investigated in a repeated design with weekly monitoring of EOtC practised during the intervention in the intervention group and control group (Month 4 to Month 14, see Table 1). Quality of delivery, variations, facilitating and limiting contextual factors at school, local, and municipality level, and teachers’ acceptability of the intervention will be investigated through semi structured interviews [81] with intervention group teachers taking place in the second half of the implementation period (Month 10, see Table 1).

#### Outcome measures

Monitoring of the intervention, namely the degree and the characteristics of the EOtC implementation, will be measured with a short self-report teacher questionnaire distributed weekly to teachers by SMS every Friday during the implementation period. In the previous TEACHOUT study, non-intended EOtC implementation in the control group was found to be 1.64 h a week [39]. The questionnaire assesses the amount, place, mode of transportation, and school subjects used during EOtC sessions. The questionnaire is based upon the existing and validated EOtC implementation monitoring tool from the TEACHOUT study [38, 39].

### Background descriptive measures

Perceived child health status and data on socioeconomic status (parents’ or legal guardian’s education level and occupational status) will be collected using the Danish Occupational Social Class Measurement [82] with the pupils’ parents (or legal guardian) (Month -2, see Table 1).

Quantitative data about teachers previous work experience and previous experience with their use of EOtC will be collected from the intervention and control group teachers (Month 0, see Table 1).

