### Recruitment and participants

We aimed to recruit ~ 54 classes (~ 81 teachers) from 30 Danish general (non-special need) education elementary schools; on average 1.8 classes per school, 1–2 teachers and 21 pupils per class, with a total of 1.134 pupils aged 10–16 years (see Fig. 3). Pupils with noteworthy health problems, reported by their parents or legal guardian, teachers, or investigators will be excluded from the analyses.

Schools in municipalities with larger proportions of citizens with lower levels of education than the average for the region were strategically invited for enrolment in the study. Schools located in the Capital Region and Region Zealand were invited to begin with. Thereafter, schools in Region of Southern Denmark were invited, and finally invitations were distributed nationally via teacher networks. School classes were not allowed to be involved in other school development or research projects.

Recruitment and enrolment started around two years before the implementation of the intervention and continued until randomisation (month − 18 to 0, see Table 1). Teachers were recruited via both municipal school directors and direct contact to local school principals. Municipalities and schools were initially contacted via e-mail and non-responders were then contacted via telephone. Online information meetings were held with school principals and teachers. Participating teachers informed the parents and were provided with written material available in Danish and English, and supplementary video material introducing the study (see Supplementary Information, Additional files 1, 3, and 4). Parents were given a letter with additional information about the study’s rationales and background, and an analogue consent form. The recruitment process was supported by general information on the MOVEOUT study project website (www.moveoutstudy.dk) [57].

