### Randomisation

Randomisation was performed by PE and MB on 1st of April 2022 (Month 0, see Fig. 4), and was made public on YouTube (see Supplementary Information, Additional file 1). Immediately after, the enrolled schools and teachers were informed by e-mail about the result of the randomisation process.

To ensure a balanced representation of grade levels across the intervention and control groups, stratified block randomisation in a 1:1 ratio was used (i.e., schools with participating classes in grade 4–6 and schools with classes 7–10 were randomised block wise in RStudio using the ‘dplyr’ and ‘readxl’ packages).

Due to the type of the intervention, it was not possible to blind the participants to group allocation. However, allocation levels will be coded before analyses and the analysts will not be informed about the codes before the final analyses have been performed.

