### Sub-study 1: effects of EOtC

#### Design

Effects of EOtC will be measured in a between-subjects design. PA measurements pre- and post-intervention will be collected in two intervals each (Test A and B) to account for seasonal variations. Data collection of the first PA pre-intervention measure commenced before randomisation and continued until just before randomisation (Pre-test A, Month -2 to -1, see Table 1). The second PA pre-measure was collected after randomisation and before the implementation of the intervention (Pre-test B, Month -1 to 0). School motivation, wellbeing, and academic achievement were measured at pre-test B.

The first PA post-measure data collection will commence during the end of the school year (Post-test A, Month 10 to 11, see Table 1). The second PA post-measure data collection will be assessed immediately before finalisation of the intervention (Post-test B, Month 11 to 12, see Table 1). School motivation, wellbeing, and academic achievement will be measured at post-test B.

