#### Statistical analyses

Estimation of intervention effects (H1, H2, and H3 of Sub-study 1) will be computed using a ‘per-protocol’ analysis [67]. All classes in the intervention group not adhering to the classification of ‘regular EOtC’ (an average of > 150 min of weekly EOtC over the school year) and all classes in control group practicing too high amount of EOtC (average of > 150 min of weekly EOtC over the school year) will be excluded. These analyses will be complemented with sensitivity analyses, following the principle of ‘intention-to-treat’ [67] which will include all schools in the analyses irrespective of their adherence to the intervention or control condition.

Linear mixed models (LMM) will be used to analyse how post-test scores varies as a function of whether the pupils were assigned to the intervention or the control group while taking into account pre-test scores, sex, age, and random effects of classes and schools. Please, see the H1 and H2 pre-registration for further information on the pre-processing steps and statistical modelling used for these data [51]. The base model used to assess H3 (effects on school motivation, wellbeing, and academic achievement) will include baseline as a covariate and school and class ID as random factor, and group allocation as the fixed effect of primary interest. Follow-up stepwise modelling will be used to investigate the contribution of previously shown confounders, i.e. primarily the number of weekly EOtC sessions [26], age, and sex [23, 68, 69], to the base models. All sub-studies will be reported following the CONSORT statements and flowchart [70].

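### Parental education and occupation are scheduled before randomisation but not named in the H3 models, which gives up some precision and leaves the main per-protocol comparison unadjusted for social background

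*Protocol article*

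**What the plan says.** Under Background descriptive measures, the article schedules "Perceived child health status and data on socioeconomic status", the latter being "parents’ or legal guardian’s education level and occupational status) will be collected using the Danish Occupational Social Class Measurement". The timing is given as "or legal guardian) (Month -2, see Table 1". Table 1 lists a parent survey of socioeconomic status twice, once in the enrolment column and once in the Pre-test A column (-2 months). Both precede randomisation, which took place "on 1st of April 2022 (Month 0, see Fig. 4". The only use indicated is the heading itself, "Background descriptive measures".

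Sub-study 1, Statistical analyses, says the linear mixed models take into account "pre-test scores, sex, age, and random effects of classes and schools". The H3 base model is then given as the baseline score, group allocation and random school and class effects. Weekly EOtC sessions, age and sex are examined in follow-up stepwise modelling, and that list is introduced as the primary confounders rather than a closed set. For H1 and H2 the reader is sent to a pre-registration. The main analysis is per protocol, with classes in either arm excluded on their average weekly EOtC minutes over the year (cut-off 150). Intention-to-treat is the sensitivity analysis.

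On recruitment, "Schools in municipalities with larger proportions of citizens with lower levels of education than the average for the region were strategically invited", first in two regions, then a third, then nationally through teacher networks. Randomisation was stratified by grade band only.

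On the H3 baseline, Sub-study 1, Design, says "School motivation, wellbeing, and academic achievement were measured at pre-test B".

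**The concern.** A social background variable scheduled before allocation is available, yet the H3 models do not name it. The follow-up list does name weekly EOtC sessions, which is a consequence of allocation. Reading and maths are the outcomes for which parental education is most plausibly prognostic. With about 15 schools per arm and stratification by grade band alone, social background can differ between arms by chance.

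Two things are at stake. Under intention-to-treat it is precision, together with the face validity of a comparison in which the arms may differ visibly on parental background. Under the per-protocol analysis it is more than precision. Classes are removed according to EOtC delivered, and if delivery is related to the social make-up of the class or school, the remaining arms may differ systematically and not only by chance.

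**Working it through.** **1. Inputs.** From Sample size: about 30 schools, 51 classes, 867 pupils (867/51 = 17 per class); ICC 0.046 for classes and 0.035 for schools; one-tailed test, 95% power, stated d = 0.374 with limits 0.187 and 0.561. From Data processing: significance level 0.05. From Randomisation: 1:1 by school.

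**2. The plan's own figure.** For a three-level design randomised at school level with no covariates,

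SE = √{4[ρ_school/schools + ρ_class/classes + (1 − ρ_school − ρ_class)/pupils]}, and MDES = 2 × t(0.95; 28 df) × SE = 2 × 1.701 × SE.

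- With 30 schools, 54 classes (1.8 per school) and 54 × 17 = 918 pupils: SE = √{4[0.035/30 + 0.046/54 + 0.919/918]} = 0.1099. MDES = 0.374, with limits 0.374 ± 1.701 × 0.1099 = 0.187 and 0.561. This matches the stated figures exactly.
- With the stated analytical sample of 51 classes and 867 pupils: SE = √{4[0.035/30 + 0.046/51 + 0.919/867]} = 0.1119 and MDES = 0.381. Power at d = 0.374 is 94.7%.

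The match needs every R² to be zero. The stated power therefore relies on no covariate and is not weakened by leaving parental background out.

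**3. Precision gained beyond the pre-test.** The documents give no R² for parental background, so the shares below are assumptions. Each is the share of variance left after the pre-test that parental background explains. Each variance component is multiplied by (1 − share).

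*(a) Same share at class and school level; relative proportions of the three components as in the stated ICCs; base SE 0.1119:*

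| Pupil share | Class and school share | SE | Reduction |
|---|---|---|---|
| 0.01 | 0.05 | 0.1098 | 1.8% |
| 0.02 | 0.10 | 0.1077 | 3.7% |
| 0.03 | 0.20 | 0.1036 | 7.4% |

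*(b) Pre-test assumed to explain 50% at every level, so base SE = 0.1119 × √0.5 = 0.0791 and MDES = 0.269 (27 df; 26 df once parental background is added):*

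| Pupil share | Class share | School share | SE | MDES | MDES reduction |
|---|---|---|---|---|---|
| 0.005 | 0.02 | 0.05 | 0.0781 | 0.266 | 1.2% |
| 0.01 | 0.05 | 0.10 | 0.0769 | 0.262 | 2.7% |
| 0.02 | 0.10 | 0.20 | 0.0746 | 0.255 | 5.5% |
| 0.03 | 0.20 | 0.30 | 0.0716 | 0.244 | 9.3% |

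The two sets together give a gain of roughly 1-9%. The article does not say which outcome the ICCs come from, so applying them to reading and maths is a further assumption.

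**4. Chance imbalance.** The difference between two means of 15 schools has standard deviation √(2/15) = 0.37 school-level SDs. This holds for any school characteristic. It is the imbalance before pre-test adjustment, not what remains after it.

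**5. Per-protocol exclusions.** Evaluation of implementation reports that control classes in the predecessor study averaged 1.64 h of EOtC a week, that is 1.64 × 60 = 98 minutes against the 150-minute cut-off. Exclusions in the control arm as well as the intervention arm are therefore plausible. The documents do not say how many classes would go, or whether delivery tracks social background, so the resulting imbalance cannot be sized.

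**The case against.** The strongest reply is that nothing here is an error. The descriptive listing and the covariate list do not conflict. In a randomised comparison with a linear model, an omitted baseline covariate costs precision and nothing else. The pre-test will carry most of what parental background could explain, and every R² above is assumed. All of that stands for the intention-to-treat analysis, and it is why this is an optional improvement.

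Several stronger readings are tempting and are not supported:

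- *That parental background is missing from all the effect models.* H1 and H2 modelling is deferred to a pre-registration that is not shown, and the follow-up confounder list for H3 is left open. What can be said is that the article does not prespecify the variable for H3.
- *That it is held for all families.* The article says only that it is collected from parents or guardians, and gives no response rate.
- *That schools will differ widely in social background.* No distribution is given, and inviting lower-education municipalities first could narrow the spread as easily as widen it.
- *That the H3 pre-test is compromised, making parental background the clean substitute.* The Design text puts Pre-test B after randomisation, but labels it Month -1 to 0, and Table 1 places it at -1 month with allocation at 0. The passages disagree. On either reading it preceded EOtC teaching, and nothing in the documents shows that test scores shifted on account of allocation.
- *That the gain is 11-20%.* Figures of that size arise only in an analysis without the pre-test (assumed shares of 5-10% at pupil level and 30-50% at class and school level), and none is planned.

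What the reply does not answer is the per-protocol main analysis. The argument that omission is harmless rests on intact randomised groups, and those exclusions break them.

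**Conclusion.** The point holds in a limited form. Parental education and occupational status are scheduled before randomisation and are not named in the H3 models; for H1 and H2 this cannot be judged from the article. The intention-to-treat estimate is not biased by the omission, and the stated detectable effect and power are unaffected. The loss is a standard error some 1-9% larger than it need be, conditional on the assumed R² values and on the stated ICCs carrying over to the H3 outcomes.

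The better reason to act is the per-protocol comparison, which is the main analysis and selects classes on EOtC delivered after randomisation. There, social background is a possible confounder that the described models do not address beyond what the pre-test captures. Its size and direction are unknown. Adjustment would deal only with the measured part, and it does not restore the protection of randomisation.

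**What to change.** Prespecify parental education/occupation class as a fixed covariate in the H3 models, with a 'not reported' category so that no pupil is dropped, in both the per-protocol and the intention-to-treat analyses. Do the same for H1 and H2 if the pre-registration does not already include it. The cost is one covariate whose collection is already planned and a few degrees of freedom. The small downside is survey non-response: adjustment is incomplete for pupils coded 'not reported', so the size of that category should be reported by arm.

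Separately, reconcile the Sub-study 1 Design text with Table 1 on whether Pre-test B came before or after allocation, since it is the only H3 baseline.

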### Data processing

All analyses will be processed in either RStudio or IBM® SPSS® Statistics with the level of statistical significance for all tests set to < 0.05.

### Trial status

Recruitment and enrolment were initiated two years before the implementation of the intervention and continued until randomisation (Month -18 to 0, see Table 1). The trial is progressing according to the time plan.

## Discussion

EOtC holds promise for improved health and education if implemented regularly and extensively. The threshold, if there is one, for ‘how much’ EOtC is required for health and education gains is uncertain, but previous experience and findings point to five hours a week as a minimum. However, this current understanding of EOtC rests on findings from previous studies (e.g. [24, 27, 29]) with inherent risks of bias. The MOVEOUT study investigates the effects of the intervention developed and conducted in the TEACHOUT study [38] with updated and strengthened design and measures. The foremost strengths and limitations of the MOVEOUT study are discussed below.

The MOVEOUT study aims to reach more solid conclusions of the effects and mechanisms of EOtC using randomised group allocation, quantification of the pedagogical and didactical elements that are posited to carry effects, and extensive monitoring. The study will not only be able to confirm or disconfirm previous assertions relating to EOtC, but also contribute to a deeper understanding of the so-called active ingredients. Pending the findings, the combination of these data sources provides considerable prescriptive potential for practice and policy.

The use of randomisation will minimise any influences on effect measures of teachers’ having different initial interest in and abilities for EOtC. It can be expected that being randomised to do what you as a teacher have hoped for when signing up for the study, i.e., being assigned to the intervention group, may affect pupil outcomes positively. It may also be that the teachers ending in the control group may not refrain from using EOtC. Therefore, the collected weekly monitoring data about EOtC practise among all classes in the project is important data to include in the analysis.

The MOVEOUT study enables an effect evaluation of EOtC-induced PA behaviours by having pre-intervention measures of PA in order to adjust post-intervention PA for baseline PA. We further use two pre-intervention and measures and two post-intervention measures to account for impacts of seasonal changes in weather. Such a design is seldom applied in the studies investigating the influence of comparable interventions on PA [21, 83], and will provide a more valid analysis of the intervention effect that the previous study on the effects of EOtC on PA [23].

Effectiveness and efficacy studies of educational interventions often fail to report whether and how the intervention was monitored [84, 85]. Such a lack of monitoring is also evident in outdoor activity programs [86] and is a general limitation for outdoor learning programs [87]. Lack of intervention monitoring, leads to a ‘black box’ approach to intervention studies, where implementation is not evaluated [88]. In the MOVEOUT study, such an approach is avoided by combining the quantitative monitoring with on-site observation on school days involving EOtC sessions and usual schooldays. Combined with school day specific assessment of PA and school motivation and learning environment perceptions, monitoring and observations enable an investigation of key mechanisms of EOtC.

## Data Availability

Anonymised participant-level data can be made available upon reasonable request to the corresponding author, such as verification of the research results. To comply with the European General Data Protection Regulation, and to accommodate article 10 of the Danish Act on Data Protection anonymised participant-level data will be made available on the Open Science Framework five years after the main publication of this study (link available in the reference list [51]).

## Abbreviations

BMI: Body Mass Index
EOtC: Education outside the classroom
EUR: Euro currency
HRQoL: Health-Related Quality of Life
LPA: Light-intensity physical activity
MI: Movement integration
MVPA: Moderate-to-vigorous physical activity
PA: Physical activity
RCT: Randomised Controlled Trial
SDQ: Strengths and Difficulty Questionnaire
SDT: Self-Determination Theory
SPIRIT: Standard Protocol Items: Recommendations for Interventional Trials
SRQ-A: Academic Self-Regulation Questionnaire
